***BASELINE CHARACTERISTICS***

• Described using frequency, and compared by means of Chi-square or Fischer’s tests.

***ANALYSIS OF EFFICACY*** ***AND SAFETY***

• Performed on all randomized patients who will receive at least one dose of chemotherapy with a use of a modified Intent-to-Treat (mITT) approach.

• Survivals and median follow-up will be estimated by the Kaplan-Meier and reverse Kaplan-Meir methods.

• Response rate will be presented with corresponding 95% CI for the median.

• Treatment outcomes will be compared using a log-rank test.

• Proportional hazard assumptions will be based on Schoenfeld residuals.

• TUDD will be evaluated using the Kaplan-Meier method.

**REASONS FOR EARLY CESSATION OF TRIAL:** Not applicable.

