S1B : English version

**FOLFOX4 versus sequential dose-dense FOLFOX7 followed by FOLFIRI in patients with resectable metastatic colorectal cancer. A GERCOR randomized phase III study (MIROX).**

Sponsor: GERCOR

Coordinator Principal: [name]

[name], Service d’Oncologie Médicale, Centre Hospitalo-Universitaire, [name], [contact], [contact], Email: [[contact]](mailto:[contact])

The United States National Health Institute registry identifier: NCT00268398.

**TRIAL DESCRIPTION**: Open-label, randomized phase III trial.

**PURPOSE**: To determine whether a sequential chemotherapy of 5-fluorouracil (5-FU)/leucovorin (LV) with dose-dense oxaliplatin (FOLFOX7) and irinotecan-based 5-FU/LV (FOLFIRI) is superior to FOLFOX4 in patients with resectable metastases from colorectal cancer (CRC).

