**ENDPOINTS EVALUATION**

• DFS defined as the interval between randomization and first evidence of relapse (local, regional, metastases or second CRC), or death from any cause.

• OS defined as the interval between randomization and patient death from any cause.

• Toxicity assessed according to the National Cancer Institute Common Toxicity Criteria (NCI-CTC) criteria, version 2.0.

• Tumor response (complete response, partial response, stable disease, progressive disease), ORR and disease control rate assessed according to the RECIST 1.0 criteria.

• HRQoL assessed using the European Organization for Research and Treatment of Cancer (EORTC) self-administered Quality of Life Questionnaire (QLQ-C30) at baseline and at 8, 16 and 24 weeks.

• Time until definitive deterioration (TUDD) used for longitudinal analyses defined as the interval between randomization and the first observation of a definitive deterioration of QLQ-C30 score, the later including 5 points decrease in QoL score compared to the QoL score at baseline, no improvement in QoL score ≥5 points as compared with baseline or patient drop-out after ≥5 points decrease resulting in missing data or death.

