**STATISTICAL ANALYSIS:**

***POWER OF TRIAL AND CLINICAL JUSTIFICATION***

• According to hypothesis that the 2-year DFS might be improved from 30% with FOLFOX4 chemotherapy to 45% with FOLFOX7-FOLFIRI (Hazard Ratio [HR] of 0.66), 15% difference using a 80% power and bilateral α type I error of 5%, 188 events is required. Based on estimated 36 months inclusion duration, and 24 months follow-up, at least 248 patients has to be enrolled. Assuming a drop-out rate around of 20% (disease progression before surgery, R2 resections or lost to follow-up), a total number of 284 patients, 142 per treatment arm, will be required.

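### Efficacy is analysed only in patients who start chemotherapy, so the primary comparison in this open-label superiority trial is not fully protected by randomization

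*Protocol*

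**What the plan says.** The Protocol, under the heading on analysis of efficacy and safety, defines the analysis set for both purposes in one line: "Performed on all randomized patients who will receive at least one dose of chemotherapy". It labels this a modified intention-to-treat approach. No analysis of all randomized patients appears anywhere in the document, not even as a sensitivity analysis.

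Three other places bear on this choice:

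- The trial description reads "Open-label, randomized phase III trial", and the stated purpose is to show superiority of the sequential regimen.
- Under endpoints evaluation, the primary endpoint starts at randomization: "DFS defined as the interval between randomization and first evidence of relapse", with death from any cause also counted. The main secondary endpoint does the same: "OS defined as the interval between randomization and patient death from any cause".
- The drop-out allowance of about 20% in the power section names progression before surgery, R2 resection and loss to follow-up. Never starting chemotherapy is not named, and no expected number of non-starters is given.

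**The concern.** Randomization makes the two arms comparable as allocated. A condition that can only be met afterwards, by someone who may know the allocation, can undo part of that. Here the condition is receipt of a first dose. The regimens differ in oxaliplatin dose and 5-FU/leucovorin schedule from cycle 1, and in the later switch to FOLFIRI, so willingness to start may differ between arms. If those who decline, or from whom treatment is withheld, have a different prognosis from those who start, the dosed groups are no longer comparable.

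The set also fits poorly with the endpoints. A patient who relapses or dies after randomization and before cycle 1 has a DFS event by the protocol's own definition, yet is removed from the analysis that counts DFS events.

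At stake is the validity of the primary DFS comparison and of OS. The direction cannot be known in advance. The exclusion is not needed either, because relapse and death can be observed in patients who never start.

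**Working it through.** **The plan's own figure.** Inputs from the power section: HR 0.66, two-sided 5%, 80% power. Freedman's formula gives (1.960 + 0.842)² × [(1 + 0.66)/(1 − 0.66)]² = 187.1, rounded up to 188, as stated. (Schoenfeld's formula gives 182 at HR 0.66.) The event target is sound on its own terms and is not the issue here.

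**Is power the issue?** No. Assume exponential DFS, uniform accrual over 36 months and 24 months' further follow-up, with no other losses. The event probability in an arm is 1 − [exp(−λF) − exp(−λ(A+F))]/(λA), with λ = −ln(2-year DFS)/24, A = 36 and F = 24. This is 0.861 at 30% and 0.738 at 45%, mean 0.799. Power is Φ(|ln 0.66| × √events / 2 − 1.96).

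| Excluded from 284 | Events | Power at HR 0.66 |
|---|---|---|
| 0% | 227 | 88% |
| 2% | 223 | 87% |
| 5% | 216 | 86% |
| 10% | 204 | 84% |

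**How far can the two analysis sets differ?** The planning hypothesis is that "the 2-year DFS might be improved from 30% with FOLFOX4 chemotherapy to 45% with FOLFOX7-FOLFIRI". Apply those rates to starters. Assume 10% 2-year DFS in non-starters of either arm, and let dE and dC be the non-start proportions in the experimental and control arms. Both the 10% and the proportions are assumptions; the protocol gives neither. In percentage points:

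all-randomized difference = [45(1 − dE) + 10dE] − [30(1 − dC) + 10dC] = 15 − 35dE + 20dC.

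| dE vs dC | Experimental, all randomized | Control, all randomized | Difference | Dosed set minus all randomized |
|---|---|---|---|---|
| 2% vs 1% | 44.30% | 29.80% | 14.50 | +0.50 |
| 5% vs 1% | 43.25% | 29.80% | 13.45 | +1.55 |
| 5% vs 5% | 43.25% | 29.00% | 14.25 | +0.75 |
| 1% vs 5% | 44.65% | 29.00% | 15.65 | −0.65 |

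The 5% vs 5% row shows how to read the last column. With equal non-start and equal prognosis of non-starters there is no selection by arm, yet the sets differ by 0.75 points, because 5% of each arm contributes no treatment difference (0.95 × 15 = 14.25). The last column is therefore a mixture of dilution and selection, not a measure of bias alone.

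**Selection alone, with no true effect.** Let 2-year DFS be 30% in both arms, exclude a share d from the experimental arm only, and suppose every excluded patient has relapsed or died by 2 years. DFS in those remaining is 0.30/(1 − d), and the apparent HR is ln[0.30/(1 − d)]/ln 0.30.

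| d | Remaining 2-year DFS | Apparent HR |
|---|---|---|
| 2% | 30.6% | 0.98 |
| 5% | 31.6% | 0.96 |
| 10% | 33.3% | 0.91 |

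If the excluded patients have the same prognosis as the rest, the HR stays at 1.00.

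**Type I error.** This was simulated with log-rank tests, 142 per arm and 4,000 runs per setting. Poor-prognosis patients at three times the hazard were present in both arms but excluded from the experimental arm only. Two-sided rejection was about 5%, 6% and 10% at 2%, 5% and 10% excluded. Rejections favouring the experimental arm were about 3.5%, 5% and 9%, against a nominal 2.5%. Runs with nobody excluded gave 5.0% and 5.7% two-sided, so the 2% setting cannot be told apart from simulation error on the two-sided scale. These are deliberately unfavourable settings.

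**The case against.** The strongest defence is that non-start is likely to be rare and similar in the two arms. Both arms receive active chemotherapy for 12 cycles in total and begin with 5-FU, leucovorin and oxaliplatin; irinotecan enters only after six FOLFOX7 cycles. Imaging within two weeks before inclusion makes relapse found between randomization and first dose less likely. A dosed-only set is proper for safety. An analysis plan that is not at hand might add an intention-to-treat analysis.

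Much of this stands, and it limits the size. It does not justify the choice. The protocol does not state that non-start is unrelated to allocation, and without blinding it cannot be presumed. The protocol itself names the dosed set for efficacy, so an analysis plan would have to depart from it.

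Three stronger readings are tempting, and the documents support none of them:

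- A reader might infer that relapse or deterioration before cycle 1 itself differs by arm. No study treatment has been given by then, so it cannot differ through treatment. Only the decision to start or withhold can depend on the arm.
- A reader might take the 1.55 points at 5% vs 1% as the bias of the plan. That is one scenario, it includes dilution, and 1% vs 5% reverses the sign.
- A reader might infer that equal non-start makes the two analyses agree. On the same formula they still differ by 0.75 points at 5% vs 5%. That gap is dilution, not bias.

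**Conclusion.** The point holds. In an open-label superiority trial with endpoints timed from randomization, the protocol restricts efficacy to patients who start chemotherapy and provides no all-randomized analysis. The primary comparison is therefore open to selection after allocation is known.

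The size cannot be established from the documents, because they give no non-start rate. Under the assumed rates, the all-randomized difference runs from 13.45 to 15.65 points over the four scenarios, against 15 in the dosed set. With few or balanced non-starters the effect is small. Type I error is clearly inflated only when about 10% are lost from one arm alone and those lost have a much worse prognosis. The documents do not show that a material bias will occur, or that it would favour the experimental arm. The wording of the analysis set is certain; the harm is conditional. This should be changed because the remedy is simple, not because the trial would otherwise be invalid.

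**What to change.** Make the primary DFS and OS analysis intention-to-treat: all 284 randomized patients, in the arm to which they were randomized. Keep the at-least-one-dose set for safety and as a sensitivity analysis of DFS. Report the number of non-starters by arm, with reasons.

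The costs are these:

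- A change of wording in the efficacy and safety section.
- Continued DFS and OS follow-up of non-starters, and of patients who leave for R2 resection or progress before surgery. The treatment plan takes R2 patients off the study, and both groups are counted in the drop-out allowance. They may well outnumber the non-starters, and the protocol should say that they stay in follow-up for DFS and OS.
- Some dilution of the effect. The 30% vs 45% hypothesis is stated by regimen without restriction to starters, so 188 events and 284 patients can stand. If the sponsor regards those rates as applying to starters only, an approximate conversion, HR = ln(experimental)/ln(control), gives 0.663 without non-starters, 0.673 at 2% vs 1% and 0.692 at 5% vs 1%. By the power formula above, 188 events then give about 80%, 78% and 71%. The roughly 227 events expected if all 284 are followed give about 87%, 85% and 79%.

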**RANDOM ASSIGNEMENT AND STRATIFICATION**

• Random assignment will be centralized and performed using an Interactive Voice Response System.

• Stratifying by:

- Treatment chronology (perioperative *vs.* postoperative chemotherapy),
- Type of local therapeutic intervention (surgery *vs.* radiofrequency ablation +/- surgery,
- Blumgart’s score (0-1 *vs.* 2-3 *vs.* 4-5).

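### Randomization is stratified on three factors, but the planned log-rank test names no strata; stratifying it costs little and protects power if the factors are strongly prognostic

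*Protocol*

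**What the plan says.** Under RANDOM ASSIGNEMENT AND STRATIFICATION the protocol lists three factors:

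- "Treatment chronology (perioperative *vs.* postoperative chemotherapy" (2 levels);
- "Type of local therapeutic intervention (surgery *vs.* radiofrequency ablation +/- surgery" (2 levels);
- Blumgart's "score (0-1 *vs.* 2-3 *vs.* 4-5" (3 levels).

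Together they define 2 × 2 × 3 = 12 cells.

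Under ANALYSIS OF EFFICACY AND SAFETY the comparison is given in one sentence: "Treatment outcomes will be compared using a log-rank test". No strata, covariates or adjusted model are named, and the test is called neither stratified nor unstratified.

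Under POWER OF TRIAL AND CLINICAL JUSTIFICATION the hypothesis is that "2-year DFS might be improved from 30% with FOLFOX4 chemotherapy to 45% with FOLFOX7-FOLFIRI" ("Hazard Ratio [HR] of 0.66"), and the trial is sized "using a 80% power and bilateral α type I error of 5%, 188 events is required". No prognostic effect or expected prevalence is given for any stratification factor.

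**The concern.** Stratified assignment removes most of the chance imbalance between arms on the three factors. A plain log-rank test computes its variance as if that imbalance could still occur. If the factors drive outcome, the test statistic then varies less than a standard normal, so the test rejects too rarely under the null. It also targets the marginal effect, which lies closer to 1 than the effect within strata.

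There is reason to expect some prognostic effect. Stratifying on a three-level score presumes that outcome differs by level. The chronology groups also differ in structure: patients operated before entry must have had an R0 resection, whereas progression before surgery, which the sample-size section counts as drop-out, can arise only in patients randomized before surgery. What is at stake is power, and consistency between design and analysis. There is no added risk of a false positive.

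**Working it through.** **1. The plan's own figure.** Freedman's formula at HR 0.66, two-sided 5%, 80% power:

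events = (1.960 + 0.842)² × [(1 + 0.66)/(1 − 0.66)]² = 187.1, rounded up to 188.

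This matches the protocol. (Schoenfeld's formula gives 182 at HR 0.66, and 187 at the unrounded ln 0.45/ln 0.30 = 0.663.) Neither formula has a term for strata, so the effect of stratifying the test has to be simulated.

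**2. Inputs from the protocol.** 284 patients allocated 1:1, 36-month accrual, analysis at 188 events, HR 0.66 (applied within strata), 12 cells.

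**3. Inputs assumed, because the protocol gives none.** Permuted blocks of 4 within cell; exponential DFS; score levels 30/50/20%; 40% in one chronology group; 15% in one local-intervention group. Factor effects are hazard ratios per score level / chronology / local intervention.

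**4. Results.** Run A used 8,000 trials per scenario (simulation error about 0.5 point on power, 0.25 on type I error). Run B used 5,000 (about 0.6 and 0.3) and added a 6-cell test on score × chronology.

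| Assumed effects | A: plain power | A: 12-cell power | A: plain type I error | B: plain power | B: 6-cell power | B: 12-cell power |
|---|---|---|---|---|---|---|
| 1/1/1 (none) | 80.6% | 77.9% | 5.2% | 80.5% | 79.6% | 79.1% |
| 1.3/1.1/1.2 (weak) | 80.0% | 78.3% | 5.0% | 80.3% | 79.8% | 79.0% |
| 1.5/1.2/1.3 (moderate) | 78.9% | 78.8% | 3.9% | 77.5% | 79.8% | 78.6% |
| 2.0/1.3/1.5 (strong) | 72.7% | 78.5% | 3.4% | 73.1% | 79.1% | 78.5% |
| 2.5/1.5/1.5 (very strong) | 65.9% | 78.0% | 2.5% | 66.7% | 78.4% | 77.5% |

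Type I error of the 12-cell test in run A was 4.8 to 5.4%; that of the 6-cell test in run B was 4.6 to 5.3%. A further simulation of the 6-cell test (error about 0.8 point on power) gave plain versus stratified power of 81 vs 80% (none), 79 vs 79% (weak), 78 vs 80% (moderate) and 72 vs 79% (strong), with plain type I error of 3.6% in the strong case.

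**5. Mechanism check.** Under the null in the strong scenario of run A, the plain statistic had standard deviation 0.920. Then 1.96/0.920 = 2.13, and the two-sided normal tail beyond 2.13 is about 3.3%, in line with the simulated 3.4%.

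**6. Gain or loss from stratifying.**

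- 12 cells (run A): 77.9 − 80.6 = −2.7 points (none), −1.7 (weak), −0.1 (moderate), +5.8 (strong), +12.1 (very strong).
- 6 cells (run B): −0.9, −0.5, +2.3, +6.0, +11.7.

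**7. Sparse cells.** With the assumed prevalences, the smallest of the 12 cells expects 284 × 0.20 × 0.40 × 0.15 = 3.4 patients. The smallest of the 6 expects 284 × 0.20 × 0.40 = 22.7.

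**The case against.** **The protocol never says unstratified.** A reader might infer that an unstratified test has been chosen. The text does not say so: a stratified log-rank test is also a log-rank test, and the choice of strata is commonly left to a SAP, which was not available here. This stands as a limit on the point. Still, the sentence fixes the test for all treatment outcomes in a section that goes into other detail (reverse Kaplan-Meier, Schoenfeld residuals), and a bare log-rank test is ordinarily read as the plain one.

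**The planned power is not shown to fail.** A reader might infer that the trial falls short of its 80%. That shortfall appears only when HR 0.66 is set within strata. The protocol's hypothesis is marginal, 30% versus 45% at 2 years. A simulation calibrated to those rates used 248 patients, 188 events, 3,000 runs and error of about 0.7 point. It assumed score prevalences of 30/50/20%, 50% perioperative and 15% radiofrequency ablation. Score hazards were 0.6/1/1.8 with 1.3 for the other two factors (moderate), or 0.5/1/2.0 with 1.4 (strong). Plain power was 80% (none), 81% (moderate) and 81% (strong); stratified power was 77%, 83% and 86%. So the objection stands as to the planned figure, while a relative gain of about 2 to 5 points from stratifying remains when the factors matter. By the same reasoning, a marginal hazard ratio nearer 1 is a different quantity from the within-stratum one, not a biased estimate of it.

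**The size rests on assumptions.** This also stands. The protocol gives no factor effects, and with weak ones the plain test is not conservative and does slightly better.

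**Twelve cells are too many.** Correct as a caution. It argues for a pooling rule, not for ignoring the factors.

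**Conclusion.** The design stratifies on three factors and the stated comparison uses none of them. Read as a plain log-rank test, the analysis is valid and type I error is not inflated. If the factors are strongly prognostic (assumed hazard ratio of 2.0 per score level, with 1.3 and 1.5 for the others), type I error falls to about 3.5% and power is about 6 to 7 points below a stratified test when the effect is set within strata. The gap is about 12 points only under the most extreme effects tried. With null or weak effects the tests are within about 1 to 3 points, the plain test slightly ahead of the 12-cell one.

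The documents do not support calling the plan's test conservative or underpowered as a fact, since that depends on effects they do not report. Nor do they support calling the 188 events or 80% power wrong. The case for change is asymmetry: the 6-cell test stays at about 78 to 80% power throughout run B, whereas the plain test ranges from about 80% to 67%. This is a cheap improvement, not the correction of an error.

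**What to change.** In ANALYSIS OF EFFICACY AND SAFETY, state that the main log-rank tests of DFS and OS are stratified by the randomization factors as recorded in the IVRS. Pre-specify how sparse cells are pooled, for example by using score × chronology (6 cells). Report the treatment effect as a hazard ratio from a Cox model with the same strata, and keep the unstratified test as a sensitivity analysis. If a SAP already says this, the protocol sentence need only be brought into line with it.

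The cost is wording: the factors are already collected at randomization and the sample size does not change. If the factors turn out not to be prognostic, the loss is about 1 point of power with 6 cells, or 2 to 3 points with all 12. Settling the choice before data are seen also removes a later choice between two p-values.
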